# Influence of the patient-practitioner interaction context on acupuncture outcomes in functional dyspepsia: study protocol for a multicenter randomized controlled trial

**DOI:** 10.1186/s12906-017-1869-y

**Published:** 2017-07-14

**Keywords:** Functional dyspepsia, Acupuncture, Randomized controlled trial, Augmented interaction, Limited interaction

## Abstract

**Background:**

In the treatment of functional dyspepsia, the placebo effect has been reported to be high, and the influence of the patient-practitioner relationship may be a major component of this effect. The specific and non-specific effects of acupuncture cannot be easily distinguished, and the patient-practitioner relationship may influence the total therapeutic effect in clinical practice. There have been no studies that investigate the influence of patient-practitioner relationship on acupuncture treatment for patients with functional dyspepsia.

**Methods:**

Patients with postprandial distress syndrome, a functional dyspepsia subtype, will be recruited at three hospitals (two in Korea and one in USA) for an international, multi-center, randomized, patient/assessor-blinded, clinical trial. The total anticipated sample size is 88. The participants will be randomly allocated into two groups: an augmented interaction group and a limited interaction group. Acupuncture, with total 12 acupoints, will be performed twice weekly for 4 weeks in both groups. Trained practitioners will provide an “augmented” or “limited” interaction context, as determined by random allocation. The primary outcome measure is the proportion of responders, the proportion of participants who answer “yes” to more than half of the adequate relief questions during the study. Secondary outcome measures include questionnaires for quality of life and symptoms of dyspepsia, and maximum tolerable volume of nutrient drink test. Data will be collected at baseline and following 4 weeks of acupuncture.

**Discussion:**

This study will evaluate the influence of the patient-practitioner interaction on clinical effects of acupuncture in patients with functional dyspepsia.

**Trial registration:**

CRIS Identifier: (KCT0002229).

## Background

Functional dyspepsia (FD) describes various upper abdominal symptoms, including abdominal pain, fullness, early satiety, and epigastric burning, without organic disease [1]. There is no cure for FD, and the therapeutic approach is complicated by the diversity of symptoms, and the inconsistency between symptoms and pathophysiology. While medication can be helpful in the short term, medication results in a temporary reduction of symptoms [2]. As a result, patients with FD are turning to alternative and complementary medicine, such as acupuncture [3].

The placebo effect is a non-specific improvement that occurs unrelated to the specific therapeutic regimen. Such non-specific clinical benefits can be divided into three components: the patient’s response to observation and assessment (Hawthorne effect); the patient’s response to the administration of a therapeutic regimen (placebo effect); and the patient’s response to the patient-practitioner relationship [4–6]. In patients with functional gastrointestinal disorders, up to 50% of the therapeutic effect may be due to the placebo effect [7, 8]. A study of patients with irritable bowel syndrome showed that non-specific effects could produce statistically and clinically significant outcomes, and that the patient-practitioner relationship was the most important component [9]. In patients with gastroesophageal reflux disease, an expanded patient-practitioner visit resulted in greater improvement of symptoms, when compared to a standard empathic medical visit. Complementary and integrative medicine consultations may enhance the placebo effect [10].

Specific effect and non-specific effects cannot be easily distinguished in complementary and integrative medicine. The influence of the patient-practitioner relationship could be a meaningful component of therapeutic experience. Therefore, to enhance the effect of treatment in a clinical setting, understanding the patient-practitioner relationship is required. To date, there have been no studies investigating the influence of patient-practitioner relationship on acupuncture treatment for patients with functional dyspepsia.

This study is designed to investigate the cognitive, emotional, and symbolic contextual factors embedded in the patient-practitioner relationship. These factors are assumed to modulate, and potentially amplify, the effect of acupuncture. Contextual factors include the use of emphatic attention, natural expressions of warmth and support, positive expectations, attentive listening, thoughtful silence, and appropriate touch. We believe that a patient-practitioner relationship “augmented” with positive components will more intensely modulate emotion, cognition, and reward when compared to “limited” context treatments.

Acupuncture is a suitable intervention to determine whether an expanded patient-practitioner interaction affects medical outcomes. The therapeutic encounter with acupuncture is “holistic,” since it includes the physical, mental/emotional, and spiritual dimensions of the individual. Therefore, acupuncture provides a suitable framework for an enhanced interaction. The acupuncture assessment interview can be adapted to extensively engage in physical, emotional, cognitive, existential, and social discourse, and can provide the patient with a sense of being cared for and understood.

The goal of this study is to investigate the influence of the patient-practitioner relationship on the effect of acupuncture on symptoms of patients with functional dyspepsia. We will answer the questions: What is the role for acupuncture in functional dyspepsia? What are the underlying mechanisms of acupuncture’s holistic clinical encounter? We will also compare the non-specific effects between Asian patients, who are likely familiar with acupuncture, and Western patients, through studies in both Asia and USA.

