## Methods

### Design

This study is planned as a multicenter, randomized controlled, patient/assessor-blinded, clinical trial to investigate the effect of two different patient-practitioner interactions on symptoms, and quality of life, of patients with functional dyspepsia. This study will be conducted in Kyung Hee University Hospital at Gangdong, Kyung Hee University Medical Center (Seoul, Republic of Korea), and the Massachusetts General Hospital (Boston, MA, USA), from January 2017 to May 2018. Participants will be randomized in a 1:1 fashion to receive either an augmented or limited medical visit. All participants will be treated for functional dyspepsia by acupuncture for 4 weeks (8 sessions). Symptoms and quality of life will be measured by questionnaires. The practitioner will discuss patient problems, including dyspeptic symptoms, at each visit in either the augmented or limited format. The initial visit will be video recorded after obtaining the participants’ consent. The Clinical Trial Institutional Review Board (IRB) of Kyung Hee University Hospital at Gangdong (No. KHNMCOH 2016–04–007-001), Kyung Hee University Medical Center (No. KOMCIRB – 150,914 – HR-040), and Massachusetts General Hospital (No. 2016P001981/PHS) have approved the study. The study will be carried out in accordance with the standards of the International Committee on Harmonization on Good Clinical Practice, and the revised version of the Declaration of Helsinki. This study has been registered under the identifier No. KCT0002229 at CRIS (http://cris.nih.go.kr). Figure 1 provides a study flow chart.

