### Participants

A total of 88 patients will be recruited from three centers (Kyung Hee University Hospital at Gangdong, 29 patients; Kyung Hee University Medical Center, 30 patients; and Massachusetts General Hospital, 29 patients).

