#### Acupuncture treatment

Acupuncture will be applied in the same manner in both groups. A total of 12 acupoints (Hegu [LI 4], Zusanli [ST 36], Taichong [LR 3], Quze [PC 3], Gongsun [SP 4] and Liangqiu [ST 34] bilaterally) will be used twice weekly for 4 week (8 sessions). Acupuncture will be performed as follows. The acupuncture needle will be applied to the participant’s skin. Then, after turning on the timer, the acupuncture needles will be rotated right and left for 3 s at each acupoint (total 12 acupoints). After 20 min, the timer is turned off, and the acupuncture needles will be rotated right and left for another 3 s at each acupoint, and then the acupuncture needles will be removed.

Detailed information regarding the acupuncture rationale is described in the revised STandards for Reporting Interventions in Clinical Trials of Acupuncture (STRICTA) [12] shown in Table 2.

**Table 2 Tab2:** Acupuncture treatment details based on the STRICTA (Macpherson H et al., [12]) checklist

Item	Detail
1. Acupuncture rationale	1a) Style of acupuncture - Manual acupuncture based on traditional meridian theory.
	1b) Reasoning for treatment provided, based on historical context, literature sources, and/or consensus methods, with references where appropriate - Based on the traditional meridian theory, clinical experience, and consensus by the experts in acupuncture and FD.
	1c) Extent to which treatment was varied - No additional acupoints allowed.
2. Details of needling	2a) Number of needle insertions per subject per session (mean and range where relevant) - Fixed 12 acupoints.
	2b) Names (or location if no standard name) of points used (uni/bilateral) - LI 4, ST36, LR3, PC3, SP4 and ST34 (bilateral)
	2c) Depth of insertion, based on a specified unit of measurement, or on a particular tissue level - From 5 to 30 mm.
	2d) Response sought (e.g. de qi or muscle twitch response) - ‘De qi’ sensation
	2e) Needle stimulation (e.g. manual, electrical) - Manual acupuncture
	2f) Needle retention time - Twenty minutes.
	2g) Needle type (diameter, length, and manufacturer or material) - A sterilized stainless steel needle (0.25 × 40 mm, DONGBANG ACUPUNCTURE INC., Ungcheon, Boryeong, Korea).
3. Treatment regimen	3a) Number of treatment sessions - Eight sessions.
	3b) Frequency and duration of treatment sessions - Twice weekly for 4 weeks, 20 min for each session.

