4. Other components of treatment	4a) Details of other interventions administered to the acupuncture group (e.g. moxibustion, cupping, herbs, exercises, lifestyle advice) - Advice for lifestyle habit included and no other interventions during the study allowed.
	4b) Setting and context of treatment, including instructions to practitioners, and information and explanations to patients - Participants will be informed that the acupuncture treatment is based on traditional Korean Medicine and previous studies on clinical trial.
5. Practitioner background	5) Description of participating acupuncturists (qualification or professional affiliation, years in acupuncture practice, other relevant experience) - Korean Medicine Doctors who have license and at least 2 years of experience of treating gastrointestinal diseases. They have studied acupuncture for more than 10 years and graduated university of Korean medicine. To ensure providing identical treatments, they finished 10 h of training and simulated the protocol.
6. Control or comparator interventions	6a) Rationale for the control or comparator in the context of the research question, with sources that justify this choice - No control intervention
	6b) Precise description of the control or comparator. If sham acupuncture or any other type of acupuncture-like control is used, provide details as for Items 1 to 3 above.

*LI* Large intestine meridian, *ST* Stomach meridian, *LR* Liver meridian, *PC* Pericardium meridian, *SP* Spleen meridian

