##### The state-trait anxiety inventory

The State-Trait Anxiety Inventory (STAI) [19] investigates anxiety as a psychological factor. The STAI is a questionnaire composed of the following 40 items evaluated using a 4-point Likert scale: 20 items evaluate the state of anxiety (anxiety triggered by a specific event) and 20 items identify the trait of anxiety (anxiety derived from personal characteristics). Higher scores indicate more severe anxiety. Anxiety has a significant correlation with dyspepsia [20, 21], and the effect of acupuncture on anxiety will be evaluated using the STAI.

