## Discussion

This study will provide information about the influence of patient-practitioner interaction on the effect of acupuncture in functional dyspepsia, and increase the knowledge about the placebo effect on complementary and alternative medicine treatments in functional gastrointestinal diseases. This study will also compare the non-specific effects of the patient-practitioner relationship between Asian patients, with familiarity of acupuncture, and Western patients, who may not be familiar with acupuncture. We will investigate the participants’ experience and use of complementary and alternative medicine at the baseline. The results of this study will be published regardless of outcome in an article on accordance of STRICTA guidelines.

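### The trial cannot show what acupuncture itself does, because every participant receives it, and it can estimate the Asian–Western difference only very imprecisely

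*Protocol article*

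**What the plan says.** The Background first gives the goal as the influence of the patient-practitioner relationship on acupuncture's effect. It then adds two further promises: "We will answer the questions: What is the role for acupuncture in functional dyspepsia", and "We will also compare the non-specific effects between Asian patients, who are likely familiar with acupuncture, and Western patients". The Discussion repeats the second: "This study will also compare the non-specific effects of the patient-practitioner relationship between Asian patients" and Western patients. Under Secondary outcomes, the STAI section states that "the effect of acupuncture on anxiety will be evaluated using the STAI".

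The design is described as follows:
- Design: "All participants will be treated for functional dyspepsia by acupuncture for 4 weeks (8 sessions").
- Acupuncture treatment: "Acupuncture will be applied in the same manner in both groups".
- Table 2, item 6a, on the control or comparator: "No control intervention".
- Participants: two Korean hospitals with 29 and 30 patients, and "Massachusetts General Hospital, 29 patients".
- Sample size calculation: based only on the overall contrast of 60% against 30% responders.
- Statistical analysis: lists paired tests of before against after as well as between-group tests, and takes efficacy to be the change from baseline (week 1) to the end of treatment (week 4).

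**The concern.** A trial can answer a causal question about a treatment only if some participants go without it or receive a credible substitute. Here both arms are needled identically, so the randomisation says nothing about acupuncture. The remaining evidence on its role would be change within an arm. The Statistical analysis section supplies tests for exactly that, and its sentence on efficacy can be read as meaning it. A significant before/after result on symptoms or anxiety could then be reported as an effect of acupuncture.

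The country comparison has a different problem. It is estimable, but the site numbers fixed in the article leave it very imprecise. A reader promised a comparison of Asian and Western patients could take a chance difference, or a chance similarity, as an answer.

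**Working it through.** **Role of acupuncture.** No arithmetic applies, so the statements are set side by side.
- Exposure to acupuncture is 100% in both arms, with the same points, sessions and technique. The between-arm difference therefore estimates the effect of the interaction style given acupuncture, and nothing else.
- Change within an arm combines any acupuncture effect with (a) natural course; (b) regression to the mean, since entry requires a dyspepsia score above 40 on the 0–100 scale; and (c) the observation, placebo and relationship effects that the Background itself lists. Nothing in the design separates these.
- No sample size repairs this, because the missing element is a contrast.

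**The plan's own sample size, reproduced.** Inputs from Sample size calculation: 0.60 and 0.30, two-sided α = 0.05, power 0.80.
- Unpooled variance: n = (1.960 + 0.842)² × (0.24 + 0.21) / 0.30² = 39.2, rounded up to 40 per arm, as stated. The pooled form gives 42.
- 40 × 1.1 = 44 per arm, 88 in total, as stated.
- This sizes the overall two-arm comparison only.

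**Asian–Western comparison.** Inputs: Korea 29 + 30 = 59 and US 29 (Participants). Assumptions: equal arms within country (29.5 and 14.5 per arm), the responder outcome, and a 60% v 30% effect in both countries unless stated otherwise. The article gives no expected difference between countries and does not say which outcome this comparison uses.
- Variance term per country: 0.6 × 0.4 + 0.3 × 0.7 = 0.45.
- SE of the difference between the two effects: √(0.45/29.5 + 0.45/14.5) = √(0.01525 + 0.03103) = 0.215.
- 95% half-width: 1.96 × 0.215 = 0.42, or ±42 points.
- After 10% dropout (26.55 and 13.05 per arm): SE 0.227, half-width ±44 points.
- Difference in effects detectable with 80% power: 2.80 × 0.215 = 0.60 (0.64 after dropout), about twice the whole planned effect.

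Power for a 30-point difference in effects, two-sided 5%:

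| Variance assumption | No dropout | 10% dropout |
|---|---|---|
| 60% v 30% variances in both countries | 29% | 26% |
| Korea 60% v 30%, US 45% in both arms | 27% | 25% |
| Korea 60% v 30%, US 30% in both arms | 30% | 27% |

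Simulating the last two scenarios without dropout gives 29% and 32%. If the US effect were half the Korean one (15 points against 30), power would be about 10%. Detecting a 30-point difference with 80% power would take about 380 participants at the 59:29 split (US 45% in both arms).

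There is also only one US hospital, so any difference between countries is equally a difference between that hospital and the two Korean ones.

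**The case against.** **On acupuncture.** The quoted question is one loose sentence. The sentence before it states the real goal correctly, the sample size concerns only the interaction contrast, and the Discussion does not repeat the acupuncture-role question. The primary outcome has no baseline value, so paired tests cannot apply to it. The sentence on efficacy may mean only that change scores are compared between arms. All of this is fair, and it confines the point to the stated claims and the secondary outcomes. It does not remove it: the article says the question will be answered, the STAI clause repeats the claim for a named outcome, and the analysis section does not say that efficacy is the between-arm comparison.

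**On the countries.** The article says only that it will compare. It promises no powered test, and an imprecise estimate is still a comparison. That stands.

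A reader might infer several stronger things that the documents do not support:
- *The comparison cannot be made at all.* It can be estimated, though not precisely.
- *The lack of a country or site term is a defect.* Such a term may sit in the full protocol or analysis plan, which is not shown.
- *Within-country significance tests are planned.* None is proposed.
- *Country is confounded with practitioners and language.* The article does not say who treats in Boston or in which language. Only the confounding with the hospital is documented.
- *The Background's figure of up to 50% covers natural course and observation.* It refers to the placebo effect.
- *An effect in Korea but none in the US would most likely be chance.* With identical effects, significance in Korea only has probability of about 0.68 × 0.60 = 0.41 (normal approximation, unpooled). That is common, but below one half.

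**Conclusion.** The point holds in two parts of different strength.

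The role of acupuncture, and its effect on anxiety, cannot be answered by this design at any sample size. This follows from the article's own description and needs no assumption.

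The Asian–Western comparison can be estimated but not answered reliably: the interval is about ±42 to ±44 points, and power is about 25 to 30% for a 30-point difference in effects. These figures assume balanced arms within country and the responder outcome at 60% v 30%. Another outcome would need its own figures. The confounding of country with the single US hospital would remain whatever the outcome.

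The primary comparison of augmented with limited interaction is not affected. What needs correcting is the scope of the claims and the definition of efficacy.

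**What to change.** - **Background:** delete the question on the role of acupuncture, or reword it as the role of the interaction within acupuncture treatment.
- **STAI section:** state that the between-arm effect on anxiety will be evaluated.
- **Statistical analysis:** state that efficacy is the between-arm comparison and that change within an arm is descriptive only.
- **Background and Discussion:** label the Asian–Western comparison exploratory. Report it as one arm-by-country estimate with its 95% confidence interval, and describe it as confounded with site.

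The cost is more modest claims and one extra exploratory model. Recruitment, treatment, sample size and the primary analysis stay as they are.

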## Methods

### Design

This study is planned as a multicenter, randomized controlled, patient/assessor-blinded, clinical trial to investigate the effect of two different patient-practitioner interactions on symptoms, and quality of life, of patients with functional dyspepsia. This study will be conducted in Kyung Hee University Hospital at Gangdong, Kyung Hee University Medical Center (Seoul, Republic of Korea), and the Massachusetts General Hospital (Boston, MA, USA), from January 2017 to May 2018. Participants will be randomized in a 1:1 fashion to receive either an augmented or limited medical visit. All participants will be treated for functional dyspepsia by acupuncture for 4 weeks (8 sessions). Symptoms and quality of life will be measured by questionnaires. The practitioner will discuss patient problems, including dyspeptic symptoms, at each visit in either the augmented or limited format. The initial visit will be video recorded after obtaining the participants’ consent. The Clinical Trial Institutional Review Board (IRB) of Kyung Hee University Hospital at Gangdong (No. KHNMCOH 2016–04–007-001), Kyung Hee University Medical Center (No. KOMCIRB – 150,914 – HR-040), and Massachusetts General Hospital (No. 2016P001981/PHS) have approved the study. The study will be carried out in accordance with the standards of the International Committee on Harmonization on Good Clinical Practice, and the revised version of the Declaration of Helsinki. This study has been registered under the identifier No. KCT0002229 at CRIS (http://cris.nih.go.kr). Figure 1 provides a study flow chart.

**Fig. 1 Fig1:**
[figure not shown]
Flow chart of the study

### Participants

A total of 88 patients will be recruited from three centers (Kyung Hee University Hospital at Gangdong, 29 patients; Kyung Hee University Medical Center, 30 patients; and Massachusetts General Hospital, 29 patients).

### Inclusion and exclusion criteria

#### Inclusion criteria

Patients who meet all of the following criteria will be considered for enrollment. The inclusion criteria are: Age between 20 and 65 years. Meeting the definition of functional dyspepsia, and postprandial distress syndrome, as a subtype of FD, according to the Rome III criteria [1]. A degree of dyspepsia more than 40 points on the visual analogue scale (0, no symptoms; 100, the most severe symptoms). Individuals who agreed not to begin new treatments associated with FD during the study. Participants may continue FD prescriptions, over the counter or alternative medications, and any psychological treatments, as long as they have been on a stable regimen for 30 days prior to the start of the study. Participants also agree not to change medications or dosage during the study. Voluntarily agreed and sign an informed consent form.

